#### 4.1.1.1 Study procedures under therapeutic indication

The nonavalent HPV vaccine (9vHPV or Gardasil-9™) was first authorized for marketing in Europe in June 2015, and is currently indicated in individuals from 9 years of age for the prevention of diseases caused by vaccine's 9 HPV types: genital warts (HPV6 and 11) and premalignant lesions and cancers affecting the cervix, vulva, vagina and anus (HPV 16, 18, 31, 22, 45, 52 and 58).

HPV vaccination is recommended by the Spanish Ministry of Health and is included in the National Immunization Program for 12 to 18-year-old girls and adult population at risk, including women treated with cervical excision with no age limit, and HIV-positive individuals under 26 years of age.

Therefore, adult women outside the risk population defined by the Ministry of Health are excluded from the National HPV Immunization Program. If eligible for inclusion, these women will benefit from participation in the present study by receiving 9vHPV vaccination free of charge.

Cervical, anal, vulvar and blood samples will be collected under standard clinical procedures, frequently used in gynecological practice (see section 8.2.1). Procedures described in this protocol are used to collect samples in the following clinical routine practice:

- Cervical samples: in women during their cervical cancer screening or follow-up visits, to perform cytology/HPV testing.

- Anal samples: in patients 40 years or older, testing positive for HPV16/18 in a cervical sample collected during a routine screening or follow-up visit.
- Vulvar samples: in women testing positive for HPV16/18 in a cervical sample collected during a routine screening or follow-up visits
- Blood samples: in patients before genital surgery or under other clinical circumstances that make it necessary by medical judgement.

Collection of oral samples does not belong to routine clinical practice. However, this and first-void urine sample are simple, non-invasive and innocuous procedures, and is generally well-tolerated by subjects (see section 8.2.1).

#### 4.1.1.2 *Statistical analysis*

Study data description and analysis, as well as study's population size and statistical power are detailed in section 9.

## 4.2 SCIENTIFIC RATIONALE FOR STUDY DESIGN

### 4.2.1 Rationale for Study Population

The study population is composed of two different cohorts.

**The RIFT-HPV 1 cohort.** It includes non-vaccinated adult women aged 18 years or older, positive on cervix for HPV 16 and/or 18 with non-apparent cervical lesion or with cervical intraepithelial neoplasia (CIN) 1/2 lesion on cytology or biopsy, eligible for **conservative treatment**.

Eligible women for this cohort are expected to frequently have productive cervical HPV infections (i.e., with high production of virions capable of infecting new cells) that allow the evaluation of HPV infectivity in cervical samples using the E1+E4-HaCaT essay, before and after vaccination with 9vHPV in a three-dose regimen.

Women in this cohort are generally expected to have a low prevalence of anal HPV infections (5% to 22% in women with no HPV-related pathology) and therefore, the obtention of anal samples with productive HPV infections is expected to be scarce.

**The RIFT-HPV 2 cohort.** It includes non-vaccinated adult women aged 18 years or older, positive for HPV 16 and/or HPV 18 anal test with non-apparent anal lesions or with anal lesions eligible for **conservative treatment**. Or non-vaccinated adult women aged 18 years or older, positive for HPV 16 and/or HPV 18 cervical test with vulvar premalignant lesion or condylomas, associated to HPV infection.

Eligible women for this cohort are expected to frequently have productive cervical and anal HPV infections that allow the evaluation of HPV infectivity in cervical, vulvar and anal samples using the E1+E4-HaCaT essay, before and after vaccination with 9vHPV in a three-dose regimen.

Since anal HPV infections are more prevalent in women with HPV-related cervical or vulvar/vaginal lesions (23% to 86%), this second study cohort will guarantee the obtention of anal and vulvar samples with productive HPV infections.

Oral and urine samples will be obtained from study subjects belonging to both study cohorts. HPV infectivity in oral and urine samples with productive HPV infections will be also evaluated in the same conditions as cervical, vulvar and anal samples.

The analysis performed on anal, urine, vulvar and oral samples obtained from the combination of both study cohorts will increase the statistical power of the analysis performed in cervical samples. Moreover, results on the evaluation of the impact of HPV vaccination on infective capacity of the virions present in cervical, anal, urine, vulvar and oral samples may yield valuable information about HPV infectivity in different anatomical areas that are involved in the transmission process of the virus.

Therefore, this study's results can be the necessary proof-of-concept (i.e. HPV vaccination can reduce viral infectivity and prevent viral transmission) to generate scientific evidence that 1) may endorse HPV vaccination in adult women and promote the design of more effective population-based vaccination programs for preventing cervical cancer; 2) may open the door to additional studies of HPV infectivity and transmission on male and female populations, focused on the reduction of the incidence of non-cervical anogenital and oropharyngeal cancers.

The size of the study population was calculated using the primary endpoint (reduction of HPV infective capacity after 3 doses of 9vHPV) as a reference. Accepting an alpha risk of 0.05 and a beta risk of less than 0.2 in a bilateral contrast, it is estimated that a minimum of 39 and 28 subjects for the first and second study cohorts respectively should be included in the study.

#### 4.3 VACCINE DOSE AND REGIMEN

The 0.5 mL dose of 9vHPV administered as a 3-dose regimen (Day 1, Month 2, Month 6) is based on the global efficacy, immunogenicity, and safety clinical studies that supported the licensure of the 9vHPV vaccine and is consistent with the approved dosing and product labelling of Gardasil-9™.

#### 4.4 BEGINNING AND END OF STUDY DEFINITION

The overall study begins when the first subject signs the ICF. The overall study ends when the last subject completes the last study-related telephone-call or visit, withdraws from the study, or is lost to follow-up (i.e., the subject is unable to be contacted by the Investigator).

For purposes of analysis and reporting, the overall study ends when the Sponsor receives the last laboratory result or at the time of final contact with the last subject, whichever comes last.

### 5 STUDY POPULATION

The study population is composed of two cohorts:

**RIFT-HPV 1 cohort:** non-vaccinated adult women aged 18 years or older, positive on cervix for HPV 16 and/or 18 with non apparent cervical lesion or with cervical intraepithelial neoplasia (CIN) 1/2 lesion on cytology or biopsy, eligible for **conservative treatment**

**RIFT-HPV 2 cohort:** non-vaccinated adult women aged 18 years or older, positive for HPV 16 and/or HPV 18 anal test with non-apparent anal lesions or with anal lesions eligible for **conservative treatment**. Or non-vaccinated adult women aged 18 years or older, positive for

HPV 16 and/or HPV 18 cervical test with vulvar premalignant lesion or condylomas, associated to HPV infection.

## 5.1 INCLUSION CRITERIA

Candidates are eligible for inclusion in the study if they:

- Are women, aged 18 years or older for cohort 1 and cohort 2 , attending a routine cervical cancer screening visit or gynecological visit, are positive for HPV16 and/or HPV18 have been recently diagnosed for their HPV-positivity (within the last 10 months) and meet one of the following criteria:

**RIFT-HPV 1 cohort:** non-vaccinated adult women aged 18 years or older, positive on cervix for HPV 16 and/or 18, with non apparent cervical lesion or with cervical intraepithelial neoplasia (CIN) 1/2 lesion on cytology or biopsy, eligible for **conservative treatment**.

**RIFT-HPV 2 cohort:** non-vaccinated adult women aged 18 years or older, positive for HPV 16 and/or HPV 18 anal test with non-apparent anal lesions or with anal lesions eligible for **conservative treatment**. Or non-vaccinated adult women aged 18 years or older, positive for HPV 16 and/or HPV 18 cervical test with vulvar premalignant lesion or condylomas, associated to HPV infection.

- Are judged to have no major health conditions (based on medical history, physical examination, and laboratory testing) that may compromise their capacity to comply with study procedures, as per Investigator's judgement.
- Provide written informed consent for their participation in the study.
- Provide a frequent contact telephone number as well as an alternate means of contact (such as an alternate telephone number or email) for follow-up purposes.
- Are planning to stay in their area of residence (near the study site) for the full duration of the study, so it is convenient for them to attend study visits at the site.

The following conditions ARE NOT CONSIDERED EXCLUSION CRITERIA. Therefore, candidates complying with them ARE ELIGIBLE FOR INCLUSION in the study:

- Coinfection with others HPV genotypes
- History of cervical surgery.
- History of condyloma acuminata
- History of HIV or other immunosuppressive conditions either acquired or medically induced.
- History of transplant immunosuppression.
- History of an autoimmune disease.

## 5.2 EXCLUSION CRITERIA

### 5.2.1 Medical Conditions

(The history of medical conditions will be based on the self-report or medical chart provided by the subject)

Candidates must be excluded from the study if they:

- Have any cervical lesion that requires clinical intervention within 7 months that could significantly affect cervical epithelia (and therefore, HPV viral production), such as cervical conisation (RIFT-HPV Cohort 1).
- Have a fever (defined as temperature  $\geq 37.8^{\circ}\text{C}$ ) within the 24-hour period prior to the Day 1 visit (Visit 1)\*.
- Have a history of severe allergic reaction (e.g., swelling of the mouth and throat, difficulty breathing, hypotension, or shock) that required medical intervention.
- Are allergic to any vaccine component, including aluminium, yeast, or BENZONASE™ (nuclease, Nicomedia [used to remove residual nucleic acids from this and other vaccines]). For this exclusion criterion, an allergy to vaccine components is defined as an allergic reaction that met the criteria for severe adverse event (SAE), defined as any untoward medical occurrence that results in death, is life-threatening, requires hospitalization or results in persistent or significant disability/incapacity.
- Have known thrombocytopenia or any coagulation disorder that would contraindicate intramuscular injection of study vaccine.
- Have a history of splenectomy.
- Have a history of ano-genital cancer or HPV-related head and neck cancer.
- Are pregnant at the time of signing informed consent, are planning to become pregnant within the full duration of the study.
- Have a history or current evidence of any condition, therapy, lab abnormality or other circumstance that might confound the results of the study or interfere with the subject's compliance of study procedures for the full duration of the study, such that their inclusion in the study is not in the best interest of the subject and/or may compromise fulfilment of study's objectives, by judgement of the Investigator.
- Are, at the time of signing informed consent, using recreational or illicit drugs or have had a recent history (within the last year) of drug or alcohol abuse or dependence at the discretion of the Investigator that might interfere with her capacity to comply with study procedures. Alcohol abusers are defined as those who drink despite recurrent social, interpersonal, and/or legal problems because of alcohol use.

\*: For items denoted with an asterisk it has to be comply before all visits if the exclusion criterion is met, then the visit may be rescheduled for a time when the criterion is not met.

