### 1.2.2 Schedule of Activities (SoA)

|                                             | Day 1   | Month 2
(±3 weeks) | Month 6
(±4 weeks) | Month 7
(-3 weeks/
+7 weeks
from Visit 3) |
|---------------------------------------------|---------|-----------------------|-----------------------|----------------------------------------------------|
|                                             | Visit 1 | Visit 2               | Visit 3               | Visit 4                                            |
| Sign Informed Consent                       | ✓       |                       |                       |                                                    |
| Review eligibility criteria                 | ✓       |                       |                       |                                                    |
| Urine sample and pregnancy test performance | ✓       | ✓                     | ✓                     | ✓                                                  |
| Temperature (fever ≥ 37.8°C)                | ✓       | ✓                     | ✓                     | ✓                                                  |
| Questionnaire                               | ✓       | ✓                     | ✓                     | ✓                                                  |
| Height and weight measurement               | ✓       |                       |                       |                                                    |

|                                                                                                                                                |   |   |   |   |
|------------------------------------------------------------------------------------------------------------------------------------------------|---|---|---|---|
| Medical history, past and current medication and vaccination                                                                                   | ✓ | ✓ | ✓ | ✓ |
| Gynecological examination in routine visit                                                                                                     | ✓ | ✓ | ✓ | ✓ |
| Cervical sample collection                                                                                                                     | ✓ | ✓ | ✓ | ✓ |
| Vulvar sample collection                                                                                                                       | ✓ | ✓ | ✓ | ✓ |

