##### 8.1.8.1 Preparation and Administration of Study Vaccine

Study vaccine must be stored at 2.0°C to 8.0°C protected from light, and it MUST NEVER FREEZE.

Study vaccine must be used as supplied (no dilution before administration). The vaccine vial should be thoroughly mixed before administration by gently rolling the vial between the palms of both hands for 30 seconds before withdrawing the suspension with a syringe.

Study vaccine should be a whitish, semi-translucent suspension when thoroughly mixed. If its appearance is otherwise, the dose will not be administered, and the manufacturer/provider will be contacted immediately.

Study vaccine will be administered in a 3-dose regimen at Day 1/ Visit 1, Month 2/ Visit 2 ( $\pm 3$  weeks), and Month 6/ Visit 3 ( $\pm 4$  weeks).

The 0.5ml dose contained in a single-dose vial should be withdrawn entirely using a sterile needle and syringe and administer promptly by intramuscular injection. The deltoid muscle of the non-dominant arm is the preferred site of vaccination. Study vaccine should not be administered in the buttocks area or within 2 cm of a tattoo, scar, or skin deformation.

Injections should be administered at a 90° angle into the muscle tissue using a needle long enough to ensure intramuscular deposition of study vaccine. The study vaccine should be administered in the deltoid muscle using preferably a 1.0 mL syringe (the largest allowable size is a 3.0 mL syringe) with the following needle length and gauge specifications:

- 1-inch needle, 22 to 23 gauge for subjects weighing <200 pounds (<90.9 kg).
- 1½-inch needle, 22 to 23 gauge for subjects weighing  $\geq 200$  pounds ( $\geq 90.9$  kg).
- 1½ -inch needle, 22 to 23 gauge for thigh injections.

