## 8.2 STUDY ASSESSMENTS

### 8.2.1 Sample Collection

#### 8.2.1.1 Cervical and Anal Sample Collection

One cervical and one anal sample will be collected from study subjects on each of the four study visits for assessment of infectivity in HaCaT assay, HPV DNA testing and genotyping and detection of anti-HPV antibodies. On Visits 1 to 3, cervical and anal samples will be collected before administration of the study vaccine's dose.

Cervical samples will be collected using an endocervical brush and the same procedure established for HPV-based screening tests. Anal samples will be collected using a PBS wetting cytobrush. It will be inserted into the anal canal, deep enough to ensure scraping of both rectal columnar and anal squamous cells.

Once collected, cervical and anal samples will be immediately immersed in a sterile collection tube containing 5 ml of PBS and stored at 4-10 °C for short term preservation until start of lab procedures (within 48h of collection), or at -80°C for long-term storage.

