### 8.5.3 Cervical, Anal, Urine, Vulvar and Oral Sample Collection Visits: Day 1, Month 2, Month 6 and Month 7.

On visits when cervical, anal, urine, vulvar and oral samples will be collected from the study subject, she must not have engaged in sexual activity within the 48 hours prior. See section 5.2.4 for definition of sexual activity.

The purpose of this restriction is to avoid HPV type-specific contamination of collected specimens due to sexual partner's fluids deposition.

If the subject does not meet this requirement, the study visit (including sample collection and study vaccination) should be re-scheduled.

The subject should not have her period to collect the samples. If the subject does not meet this requirement, the study visit should be re-scheduled.

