#### **9.1.1.2 Data analysis**

Differences in the infectivity rate before (Day 1/ Visit 1) and after vaccination (Month 7/ Visit 4) will be compared in cervical, anal, vulvar, urine and oral samples using non-parametric Wilcoxon signed rank test.

For cervical samples, joint and stratified analysis for HPV-RIFT1 and HPV-RIFT2 cohorts will be done.

Oral, vulvar, urine and anal samples included in the HPV-RIFT1 and HPV-RIFT2 cohorts will be analyzed together to obtain the minimal sample size established for this analysis. If sample size would allow stratified analysis for HPV-RIFT1 and HPV-RIFT2 cohorts, it will be performed and submitted.

Sensitivity analysis including only cases showing negative seroconversion before vaccination will be performed.

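### The 7-month limit on foreseen cervical interventions in RIFT-HPV 1 can end 19 to 77 days before the last in-window Visit 4, and the analysis-set rule keeps a treated, still-positive sample

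*Protocol*

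**What the plan says.** Section 5.2.1 excludes a candidate under this criterion: "Have any cervical lesion that requires clinical intervention within 7 months that could significantly affect cervical epithelia (and therefore, HPV viral production". The example given and the scope are "such as cervical conisation (RIFT-HPV Cohort 1", so the criterion applies to Cohort 1 only. The starting point of the 7 months is not stated.

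The Schedule of Activities (section 1.2.2) sets Visit 3 at "Month 6 (±4 weeks" and Visit 4 at "Month 7 (-3 weeks/ +7 weeks from Visit 3". Section 8.2.1.1 provides for cervical sampling at every visit: "One cervical and one anal sample will be collected from study subjects on each of the four study visits".

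The primary comparison in section 9.1.1.2 uses the first and last of these samples: "Differences in the infectivity rate before (Day 1/ Visit 1) and after vaccination (Month 7/ Visit 4) will be compared". Cervical samples are analysed for both cohorts together and by cohort.

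After vaccination, section 9.1.1.1.2 removes cases that are HPV16/18 DNA-negative, lack virions, lack exudated antibody or have not seroconverted. It does not mention a cervical intervention between the two samples. Section 1.2.1 states that there is no control and that the study has a single arm.

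**The concern.** The protocol itself names cervical intervention as something that changes HPV viral production, which is what the primary endpoint depends on. The exclusion is there to keep that influence out of the before-after comparison. Its horizon is a fixed 7 months, while the sample it protects can be taken later. A woman whose intervention is foreseen just after month 7 passes the criterion and could be treated before a late Visit 4.

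What happens next depends on her sample. If treatment leaves it DNA-negative or virion-negative, it leaves the analysis set and, on the loss categories in section 9.2.1, would probably be filed as clearance. If it is still positive but carries less virus, it stays in. Without a control group, nothing separates that fall from the effect of vaccination.

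**Working it through.** **Inputs.** Exclusion horizon: 7 months (5.2.1), counted from Day 1 by assumption. Visit 3: Month 6, up to 4 weeks late (1.2.2). Visit 4: up to 7 weeks late, counted from Visit 3 (1.2.2). One month = 365.25/12 = 30.44 days.

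**The plan's own figure.** Nominal Visit 4 = 6 months + 1 month = 7 months = day 213. This equals the exclusion horizon, so there is no gap on the nominal schedule.

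**Latest in-window Visit 4.** The window can be read as at most 7 weeks after Visit 3, or as a tolerance around one month after Visit 3. Six months is day 182.6 and seven months is day 213.1.

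| Reading of the Visit 4 window | Visit 3 | Latest Visit 4 | Months | Days past day 213 |
|---|---|---|---|---|
| At most 7 weeks after Visit 3 | on time | 182.6 + 49 = day 232 | 7.6 | 19 |
| At most 7 weeks after Visit 3 | 4 weeks late | 182.6 + 28 + 49 = day 260 | 8.5 | 47 |
| One month after Visit 3, plus 7 weeks | on time | 213.1 + 49 = day 262 | 8.6 | 49 |
| One month after Visit 3, plus 7 weeks | 4 weeks late | 213.1 + 28 + 49 = day 290 | 9.5 | 77 |

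The gap exists under both readings, even with Visit 3 on time.

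**Which samples stay in.** Setting 5.2.1 beside 9.1.1.1.2, a treated woman stays in the comparison only if her Visit 4 sample is still DNA-positive and virion-positive and she meets the antibody conditions. No rule shown removes her because the cervix was treated.

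**Illustration of size.** Section 9.2.1 gives 39 pairs, a 25% reduction, alpha 0.05 two-sided and beta below 0.2, but no SD or scale. On an assumed log2 scale, a 25% reduction is log2(0.75) = -0.415 cycles. The implied SD is 0.415 × √39 / (1.96 + 0.84) = 0.93, or 0.90 with the t correction. A 75% fall is log2(0.25) = -2 cycles. The 40% loss in 9.2.1 applied to 39 gives 39 × 0.6 = 23 pairs. I simulated no vaccine effect, normal differences with SD 0.90 and the two-sided Wilcoxon signed-rank test at 0.05, counting significance only in the direction of reduction (40,000 runs per cell):

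| Treated women, each with a 75% fall | 39 pairs | 23 pairs |
|---|---|---|
| 0 | 2.5% | 2.2% |
| 1 | 3.7% | 4.0% |
| 3 | 8.2% | 10.8% |

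One treated woman with a 50% fall gives 3.2% and 3.6%. The numbers of treated women are assumptions; the protocol gives none.

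**The case against.** The strongest reply is that 7 months is the study's nominal length throughout (for example the 7-month follow-up in 9.1.3), so 5.2.1 is aligned with the schedule and the gap arises only when visits run late. That stands: this is a mismatch between a nominal horizon and the permitted windows, not a flat contradiction.

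Other guards exist. RIFT-HPV 1 admits only women with no apparent lesion or with CIN 1/2 suited to conservative treatment, a criterion with no 7-month limit. Section 5.2.1 also has a general exclusion for circumstances that might confound the results over the full study. Both reduce the gap. Neither closes it: the first term is not defined, and the second rests on the investigator's judgement, made beside a specific rule that stops at 7 months.

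The path to bias is narrow. The intervention must be foreseen at Day 1, fall after month 7, precede a late Visit 4 and leave the sample positive. That argues for a modest weight. Treatment not foreseen at Day 1 is beyond any eligibility horizon, which is why the analysis-set line matters more than the eligibility wording.

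A reader might infer that re-scheduling lengthens the gap further, since 8.5.3 says of menstruation: "If the subject does not meet this requirement, the study visit should be re-scheduled". The text does not say that a re-scheduled visit may leave its window, and section 8 requires adherence to the schedule. The day counts above include no re-scheduling.

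Handling of samples taken after a procedure may also sit in a separate statistical analysis plan that is not shown. But section 9 is headed as the statistical analysis plan and lists its analysis-set rules in detail, so the line belongs beside them.

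**Conclusion.** The point holds as a moderate-to-minor inconsistency. Counted from Day 1, the exclusion horizon can end 19 to 77 days before the last in-window Visit 4 sample, and 9.1.1.1.2 would keep a treated, still-positive sample as an after-vaccination value in an uncontrolled comparison.

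A reader might go further and infer that the protocol expects treated women in the primary analysis, or that the result is materially distorted. The documents do not support that. They give no number of treated women, the number is probably small, and one such woman moves the false-reduction rate only from about 2.5% to about 4%. The 8% to 11% for three women rests on an assumed count, an assumed 75% fall and an SD back-calculated on an assumed log2 scale.

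Nor do RIFT-HPV 1 cervical samples alone carry the primary result: it covers five sample types, and cervical samples are analysed jointly across cohorts. That joint analysis widens the point in one respect, because Cohort 2 cervical samples enter it without this exclusion.

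**What to change.** 1. In 9.1.1.1.2, state that a cervical sample taken after a cervical intervention, in either cohort, is not used as the after-vaccination value in the primary comparison and is not counted as HPV clearance. This also covers treatment not foreseen at Day 1 and Cohort 2 samples in the joint analysis. Section 8.1.4 already collects new medical history after Visit 1, so the information should be at hand. The cost is one line and the loss of a few pairs.

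2. Reconcile the 7-month horizon in 5.2.1 with the Visit 3 and Visit 4 windows in 1.2.2, and state the day from which the 7 months is counted. How the passages are brought into line is for the sponsor to decide. The cost is a wording change in one or both sections. Nothing here takes a view on when any lesion should be treated.
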